#### Secondary outcome analysis

Analyses of the continuous secondary outcome scores will take a similar approach to the analysis described for the primary outcome; however, models for these outcomes will additionally include adjustment for the associated baseline measurement.

#### Economic evaluation

The incremental cost per quality-adjusted life year (QALY) gained with the NIDUS-family intervention compared to usual care will be calculated over the 12-month duration of the trial. The primary cost analysis will be from NHS and personal and social services perspective and include NIDUS-family intervention cost in the treatment arm and resource use costs in both arms [36]. The cost of the intervention will include the cost of training, supervision, and staff time to deliver NIDUS-family intervention costed at the relevant staff grade [37]. We will collect information on impact on family carers for a societal perspective analysis. Resource use on health and social care will be collected using an adapted version of the CSRI and will be costed using the most recent nationally published sources [37].

QALYs will be calculated based on participant and family carer responses to the DEMQOL/DEMQOL proxy using the DEMQOL-U/DEMQOL-U-proxy classification system [38]. QALYs will be calculated as the area under the curve adjusting for baseline differences.

Means and 95% confidence intervals for all key results will be reported. These will be calculated using bootstrapping, adjusting for baseline and including the same covariates as specified in the statistical analysis plan. In addition, missing data will be addressed as specified in the statistical analysis plan.

Cost-effectiveness planes and cost-effectiveness acceptability curves for a range of values of willingness-to-pay for a QALY gained will be reported using the bootstrapped results.

#### Qualitative analysis of interviews

After completion of final follow-up, a 10% sub sample of participants who received the NIDUS-family intervention will be interviewed to explore their experiences of receiving the intervention and to inform adaptations and improvements to the intervention for wider roll out. This should be sufficient to reach theoretical saturation. People will be purposively recruited with varying socio-demographic characteristics to comprise a maximum variation sample, and we will invite for interview those who did not complete the intervention as well as completers to gain differing opinions. NVivo software will be used for qualitative data analysis, and a thematic analytic approach to analysing transcripts will be taken [39]. Two researchers will systematically code the transcripts into meaningful fragments and label these initial codes. Discrepancies will be discussed and resolved with the investigators overseeing the trial. The researchers will then organise the data into preliminary themes. They will discuss the coding frames within the NIDUS team using the constant comparison method to identify similarities and differences in the data. Emerging analyses will also be discussed with the NIDUS PPI group. The process evaluation data collection will be led from the ARU site, who are not involved in data collection for the main trial, and they will also lead the analysis of the process evaluation data, to reduce risk of bias.

#### Quantitative evaluation of intervention acceptability

After completion of final (12 month) study outcomes, intervention participants will be asked to rate acceptability of the intervention on a 5-point Likert scale by responding to the statement ‘the intervention helped the person I care for’ with 1 indicating strongly disagree and 5 indicating strongly agree with space for free text feedback on their experience of receiving the intervention.

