#### Intervention description {11a}

The intervention is delivered over a 1 year period: 6–8 manualised sessions within the first 6 months, by video call/telephone (with potential for face to face when COVID-19 restrictions permit), followed by catch-up calls every 1–2 months (at preference of participating dyad) to review progress towards goals and troubleshoot any difficulties for the remainder of the intervention period. The manualised sessions are tailored to participant’s preferences and needs for staying independent at home. In session one, the facilitator explores the participant’s identified goals and maps them to a menu of training modules, based on their priorities and concerns around maintaining independence at home. They also explore their support networks and identify gaps, sign-posting participants to existing resources and services. The modules include information and strategies addressing the following areas:
Accepting care, arranging, and planning for the futureCommunicating with people living with dementia, family, and professionalsManaging behaviours and challenging behavioursManaging physical health conditionsExercise, activity, and mobilityManaging low mood, anxiety, and apathyCarer wellbeing and supportSafety, environment, telecare, strategies supporting functioning at homeRelaxation and stress management strategiesSleep, diet, and healthy routines

Each of these modules, if selected, is completed over 1–3 sessions; so, we anticipate most dyads will have the opportunity to complete between 2 and 4 modules. At the final appointment (the 6th, 7th or 8th session depending on the needs and preference of the dyad), the facilitator brings together old and new strategies that have worked to help the participant formulate a final action plan. They then conduct telephone calls every 1–2 months to offer support and guidance on implementing strategies and to troubleshoot any problems. Sessions are delivered to family carers and people living with dementia together or to the family carer alone. This is agreed with each dyad (depending on their goals and circumstances) so that the most appropriate arrangement is made for each session for each dyad.

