#### Primary outcome

The primary outcome is functioning of the person with dementia assessed using family carer rated Goal Attainment Scaling (GAS) at 12 months follow-up. GAS is valid, reliable, and responsive to change in function in people with dementia living at home up to 12 months [21, 22]. Trained researchers will work with family carers and people living with dementia to set SMART (Specific, Measurable, Achievable, Realistic and Time-bound) goals across domains including: cognition, instrumental activities of daily life/self-care, mood, behaviour, and mobility. Family carers will evaluate ‘performance’ of the person living with dementia (or carer wellbeing if the goal relates to this) on a minimum of three and maximum of five goals set at baseline, on a 5-point scale ranging from ‘much worse’ to ‘much better’ than expected. As people will have different goals and numbers of goals, a summary formula standardises the degree of goal attainment [21], analysed as a change score. We will calculate GAS for people with dementia who have died, using procedures outlined by Gordon et al. [32]. Where death was unexpected, attainment in each domain will be rated as − 2. Where death was expected (we exclude clients who are considered to be in their last 6 months of life, but circumstances can change and we follow-up clients for 1 year), goals will be rated as achieved prior to death.

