### Data collection and management

#### Plans for assessment and collection of outcomes {18a}

Data is collected at baseline and 6- and 12-month follow-up for all participants (Table 1). Those in the intervention group are asked to complete an additional measure on acceptability of the intervention at the end of the study. Approximately 10% of participants in the intervention group will participate in an additional qualitative interview about their experiences of receiving the intervention. All researchers are fully trained to use the data collection tools. All outcome assessments will be measured using validated questionnaires (please refer to the ‘Objectives’ section of this protocol for a list of validated questionnaires that will be used in this trial).

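### The one scored acceptability item asks whether the person with dementia was helped, so the score measures carer-perceived benefit and should not be reported as acceptability

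*Protocol article*

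**What the plan says.** The section Quantitative evaluation of intervention acceptability in the protocol article states that "intervention participants will be asked to rate acceptability of the intervention on a 5-point Likert scale". The rating is given by responding to a single statement, "the intervention helped the person I care for’ with 1 indicating strongly disagree and 5 indicating strongly agree". The same sentence adds an open part to the form, "with space for free text feedback on their experience of receiving the intervention".

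Two other places carry the acceptability label. Plans for assessment and collection of outcomes {18a} says: "Those in the intervention group are asked to complete an additional measure on acceptability of the intervention at the end of the study". Table 1, under Participant timeline {13}, lists acceptability for the intervention group at t14, the 12-month point. Neither place describes a second scored item.

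Two features of the intervention bear on the wording. Under Primary outcome, the carer rates the performance of the person with dementia, "or carer wellbeing if the goal relates to this". Under Intervention description {11a}, one module is about carer wellbeing, and "Sessions are delivered to family carers and people living with dementia together or to the family carer alone".

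**The concern.** The article names a construct, acceptability, and then states the item that is to measure it. The two do not match. Whether an intervention helped someone is a judgement about effect. Whether it was acceptable is a judgement about receiving it: the demands it made, the content, the format, and whether the dyad would have it again. A carer can hold either view without the other.

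This cannot be set aside as detail left to a fuller document, because the article itself gives the wording, the anchors and the label.

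What is at stake is one reported result. The score would appear as the trial's quantitative finding on acceptability, although it is an unblinded benefit rating from one arm. The trial already measures benefit against a comparator through GAS and the secondary outcomes. Acceptability of the format now in use is a live question. The Introduction reports that the intervention was acceptable in feasibility work with 14 dyads, and the Discussion concedes that remote delivery takes the format further from what was tested there. The Introduction also warns that engaging dyads by telephone alone may be difficult.

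**Working it through.** The article states no figure on this point, so there is none to reproduce. The check is a comparison of passages, followed by two small calculations of scale.

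**1. What the item covers, against what the label promises.**
- Benefit to the person with dementia: asked directly.
- Benefit to the carer: not asked, although a goal may be about carer wellbeing, one module is devoted to it, and some sessions may be held with the carer alone.
- Burden of the sessions and follow-up calls: not asked.
- Session format, and remote delivery in particular: not asked.
- Willingness to continue or recommend: not asked.

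**2. Who can answer.** The sentence speaks of intervention participants, but the statement is worded so that only the carer can respond. The person with dementia gives no score.

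**3. What one score cannot separate.** A carer who found the sessions acceptable but saw no help to the relative would score low. A carer who saw help but found the format burdensome would score high. The score alone does not distinguish either from a carer for whom acceptability and benefit go together.

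**4. How many scores are affected.** The Sample size section gives 198 intervention dyads (the Abstract gives 199) and allows for 15% loss. Then 198 × 0.85 = 168.3, about 168 scores. All of them come from this item. The interviews cover 10% of the arm: 198 × 0.10 = 19.8, about 20 dyads.

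**5. Whether the size of the error can be known.** Let a be the share who find the intervention acceptable, p the share of those who agree the person was helped, and q the share who agree among the rest. Then

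agreement = a × p + (1 − a) × q.

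The documents give none of the three. Purely as an assumption, take a = 0.90.
- With p = 0.70: 0.63 + 0.10 × q, which runs from 63% (q = 0) to 73% (q = 1). The score understates acceptability by 27 to 17 points.
- With p = 1: 0.90 + 0.10 × q, which runs from 90% to 100%. The score is right or overstates acceptability by up to 10 points.

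Even with a held fixed, the difference runs from 27 points too low to 10 points too high. These values show only that neither size nor direction follows from the plan. They are not an estimate.

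**The case against.** The strongest reply is that the trial does not rest its view of acceptability on this score. The same form offers free text to every responding intervention participant, and that can cover burden, format and carer benefit. Under Qualitative analysis of interviews, a 10% subsample "will be interviewed to explore their experiences of receiving the intervention and to inform adaptations and improvements to the intervention for wider roll out", and "we will invite for interview those who did not complete the intervention as well as completers to gain differing opinions". Fidelity analysis counts appointments delivered across all intervention participants. The section on discontinuing or modifying interventions {11b} has reasons for withdrawal recorded. Delivery mode is examined in a planned subgroup analysis of the primary outcome. Acceptability is not among the stated objectives, and no threshold or decision hangs on the score.

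All of this stands, and it rules out two stronger readings. A reader might infer that the trial will be unable to say anything about acceptability. The documents do not support that, because the free text, interviews, uptake and withdrawal data all bear on it. A reader might also infer that a carer whose relative declined would have to disagree with the item. That does not follow either: the statement says helped, not improved, and a carer can credit help to someone who nevertheless got worse. Decline may lower the score, but it need not.

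The reply does not make the score an acceptability score. Appointment counts are planned as fidelity data, and the subgroup analysis concerns goal attainment. The free text and interviews are not scored. The only number that carries the label still answers a different question.

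**Conclusion.** The point holds for the Likert score and no further. By itself the score measures carer-perceived benefit to the person with dementia and should not be reported as a quantitative acceptability result. It affects every acceptability score, about 168 under the plan's own loss assumption, but the error in percentage points cannot be determined from the documents.

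The consequence is minor. This is a descriptive, single-arm process measure taken after the 12-month outcomes, and no primary, secondary or economic analysis depends on it. The conclusion rests on one assumption: that the item as printed is the whole of the scored measure, which is how all three places in the article describe it.

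**What to change.** Report the existing item under the label 'carer-perceived benefit to the person with dementia', and say that the carer is the respondent.

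Add two separate 5-point items to the t14 intervention-arm form and use them as the acceptability score. For example: 'The NIDUS-family sessions were acceptable to me' and 'The way the sessions were delivered to me (telephone, video call or face to face) was acceptable to me'. They should be kept apart, because a single item on both could not separate content from remote format.

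The time to do this is before the first 12-month forms are used. The first dyad was recruited on 3 April 2020, so those forms fall due in about April 2021. The article was written in October 2020.

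If the form cannot change, relabel the existing item and draw conclusions on acceptability only from the free text, interviews, appointment counts and withdrawal reasons.

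The cost is one or two extra Likert items at an existing assessment and a minor amendment; relabelling alone costs only wording. The new items would still give the carer's view only, and burden and carer benefit would still be covered mainly by the free text and interviews.

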#### Fidelity analysis

To analyse fidelity of delivery of NIDUS-family, the number of appointments delivered across all intervention participants will be assessed. A random sample of 20% of appointments will be audio-recorded, transcribed, and checklists applied independently by two researchers. A mean fidelity score will be produced by dividing the number of items on the checklist identified as being delivered in the appointment, by the number of items on the checklist that should have been delivered. Thresholds used in other intervention fidelity work will be adopted [40]: where 81–100% constitutes high fidelity, 51–80% is moderate fidelity, and 50% or lower constitutes low fidelity.

#### Interim analyses {21b}

As this is a trial of a psychosocial intervention and the intervention is low risk, we do not plan interim analyses. Should the independent combined Programme Management Group/Data Monitoring and Ethics Committee (PMG/DMEC) consider it necessary, they will request this and liaise with the CTU and trial sponsor.

#### Methods for additional analyses (e.g. subgroup analyses) {20b}

The following supportive analyses will be carried out for the primary and secondary outcomes using the same modelling approaches as described in the ‘Statistical methods’ section of this protocol:

• Adjusted analyses allowing for other predefined factors related to the outcome (whether the family carer participating was living with the care recipient and whether the care recipient had capacity to give informed consent to participate (as an index of dementia severity)).

• Estimation of the treatment effect adjusting for any concerning imbalances in baseline characteristics.

Subgroup analyses will explore the primary outcome in (1) those who receive a minimum ‘dose’ of the intervention, relative to the control group and those who do not, and (2) between participants receiving the intervention predominantly by telephone, video call, and (if applicable) face to face (3).

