Our NIDUS-family intervention is delivered to people with dementia and family carers by NIDUS facilitators (graduate psychologists/social researchers with relevant experience but without formal clinical training) with supervision, training, and clinical oversight, so it can be widely implemented and give value if effective.

We originally planned to deliver the NIDUS-family intervention face-to-face to people in their homes; however, just before the trial started, lockdown restrictions due to the COVID-19 pandemic were imposed in the UK. Following discussion with our PPI members and project management team, we adapted delivery to online video or telephone sessions, so participants could continue to receive it until it is deemed safe for researchers to meet with participants face-to-face. We also adapted our intervention content, specifically to signpost to remote rather than face-to-face services, to acknowledge the restricted options for outdoor activity and the stresses of living through the pandemic lockdown. Most psychological interventions (NHS and research) for people living with dementia are being delivered remotely at the time of writing due to the needs for social distancing during the pandemic. This has illustrated the possibilities of remote delivery as well as challenges. Interventions can be potentially delivered in people’s homes very cost-effectively through video calling or over the telephone, and catchment areas can be widened. Not everyone has access to video calling, however, and engaging dyads over telephone alone may be particularly challenging.

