## Methods: participants, interventions, and outcomes

### Study setting {9}

We are recruiting potential participants via clinicians and research nurses working in NHS Trust memory clinics/older adult mental health services and GP practices based in London, Bradford, Leeds, Hull, Oxfordshire, Buckinghamshire, Kent, Essex, and Surrey and directly via the recruitment database Join Dementia Research and Twitter. Subsequent to protocol amendments made in response to COVID-19 and before study commencement, informed consent, outcome assessments, and intervention delivery are conducted via telephone or video call, depending on individual participant preference; prior to COVID-19 restrictions, we expected that outcome assessments and intervention sessions would be face to face, and if restrictions are lifted and it is safe to do so during our recruitment period (planned: April 2020 to February 2022), we will also offer this option to participants. At time of writing (October 2020), all trial processes have been conducted remotely. A list of study sites can be found here: https://www.ucl.ac.uk/psychiatry/research/mental-health-neuroscience-department/nidus/about-nidus-study/stream-2-nidus-family.

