#### Criteria for discontinuing or modifying allocated interventions {11b}

The intervention has been modified in response to feasibility testing in a previous study [13], and therefore, no further modifications to the intervention are planned. The intervention is currently being delivered online/by telephone as opposed to face-to-face in response to restrictions imposed by the COVID-19 pandemic to ensure participant and facilitator safety. The psychosocial intervention has been assessed as low risk; therefore, we have not set criteria for discontinuation; however, participants may decide to discontinue the intervention sessions or withdraw from the project at any point. If participants decline the intervention at any point, they will be asked if they would still wish to meet with the researchers completing outcome assessments. Although it will be stressed that participants can withdraw at any time without giving a reason, any assessments that have been collected to that point will be retained and contact with participants will be maintained unless researchers are told otherwise. All contacts with participants and reasons for withdrawing from the intervention or study will be documented on the study database.

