#### Plans to promote participant retention and complete follow-up {18b}

While face to face delivery is not possible due to COVID-19 restrictions, we will offer a choice of video call options or telephone contact where participants are unable or do not wish to use video call. Participants will be offered a £20 voucher to thank them for their time after each follow-up appointment (baseline and 6 and 12 months and qualitative interview).

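### The exploratory dose and delivery-mode analyses compare groups formed after randomisation, so they can show a difference when the intervention has no effect

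*Protocol article*

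**What the plan says.** The protocol's section on additional analyses {20b} lists supportive adjusted analyses and then a separate subgroup sentence. It opens "Subgroup analyses will explore the primary outcome in (1) those who receive a minimum" dose. Its wording on comparators and modes reads "of the intervention, relative to the control group and those who do not, and (2) between participants receiving the intervention predominantly by telephone". The other modes named are video and, should it take place, in-person delivery.

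Other sections show how dyads come to be in these groups:

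- **Dose.** Section {11b} says "participants may decide to discontinue the intervention sessions or withdraw from the project at any point". Section {11a} lets the final appointment be the sixth, seventh or eighth, according to what the dyad needs and prefers.
- **Telephone or video.** Under Study setting {9}, consent, assessments and "intervention delivery are conducted via telephone or video call, depending on individual participant preference". Section {18b} offers "telephone contact where participants are unable or do not wish to use video call".
- **Face to face.** Section {9} offers this only "if restrictions are lifted and it is safe to do so during our recruitment period".

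The primary analysis compares the arms as randomised, whatever the adherence (Primary outcome analysis, {20a}).

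**The concern.** A subgroup analysis in a randomised trial normally divides both arms by something fixed before allocation, so that the arms can be compared fairly within each level. Dose received and mode received do not meet that condition. No control dyad has a value for either, and both result partly from who the dyad is and how the year goes.

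Dyads who keep attending may be those who would have attained more of their goals anyway. Setting them against all controls removes the likely poor performers from one side only. Setting them against dyads below the dose compares two self-selected groups directly.

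The mode comparison has the same weakness within one arm, and the protocol gives a reason to expect it to matter: "Not everyone has access to video calling, however, and engaging dyads over telephone alone may be particularly challenging". A difference between telephone and video users could reflect access, skill or severity rather than mode.

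At stake is the interpretation of these results. A reader could conclude that the intervention works if completed, or that video works better, from contrasts that cannot establish either.

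**Working it through.** **The plan's own figure.** Section {14} gives an effect of 0.5 SD, 5% two-sided, 90% power, 2:1 allocation, ICC 0.05, cluster size 20 in the intervention arm, and 15% loss.

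- Design effect: 1 + 19 × 0.05 = 1.95.
- Controls before loss, normal approximation: (1.95/2 + 1) × ((1.960 + 1.282)/0.5)² ≈ 83.0.
- With the noncentral t distribution, 84 controls and 168 intervention dyads give power 0.901.
- Dividing by 0.85 gives 98.8 and 197.6, hence 99 and 198, total 297.

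The stated total reproduces. The protocol gives no figure for the subgroup analyses. The check below uses 168 and 84 dyads analysed.

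**Assumptions not in the protocol.** A share f of 60–90% of intervention dyads reaches the minimum dose. Those dyads would have scored g = 0.3–0.5 SD better than the rest without any intervention. The true treatment effect is zero.

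**Formulas.**

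- Dosed versus control: bias = g(1 − f); SE = √(1/(168f) + 1/84).
- Dosed versus below the dose: bias = g; SE = √(1/(168f) + 1/(168(1 − f))).
- False-positive rate: Φ(−1.96 + bias/SE) + Φ(−1.96 − bias/SE).
- With clustering, 1/(168f) in the control contrast is multiplied by 1 + (20f − 1) × 0.05.

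| f | g | Bias vs control (SD) | False positives vs control | Same, with clustering | Bias vs below dose (SD) | False positives vs below dose |
|---|---|---|---|---|---|---|
| 0.60 | 0.3 | 0.12 | 12.8% | 11.2% | 0.30 | 47.8% |
| 0.60 | 0.5 | 0.20 | 27.3% | 22.8% | 0.50 | 88.8% |
| 0.75 | 0.3 | 0.075 | 8.3% | 7.6% | 0.30 | 39.1% |
| 0.75 | 0.5 | 0.125 | 14.4% | 12.3% | 0.50 | 80.1% |
| 0.90 | 0.3 | 0.03 | 5.6% | 5.4% | 0.30 | 21.5% |
| 0.90 | 0.5 | 0.05 | 6.6% | 6.2% | 0.50 | 49.4% |

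Example for f = 0.6, g = 0.5: bias 0.5 × 0.4 = 0.20; SE √(1/100.8 + 1/84) = 0.148; false-positive rate 27%.

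**If one pooled comparator is meant** (controls together with dyads below the dose), the bias lies between the two columns. For f = 0.6, g = 0.5, dyads below the dose average −0.5 × 0.6 = −0.30, so the bias is 0.20 + 0.30 × 67.2/(84 + 67.2) = 0.33 SD.

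**Second model.** Let the tendency to attend correlate 0.1–0.3 with outcome, with attendance set by a threshold on that tendency (truncated normal, 4,000 simulated trials per setting, no clustering). For f from 60% to 90%, the bias is 0.02–0.19 SD against control, with 5–27% false positives, and 0.16–0.59 SD against those below the dose, with 12–88%. The two models agree closely.

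**Mode.** The protocol gives no basis for a figure. This part rests on the statements that mode follows preference and ability, and that no control dyad has a delivery mode.

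**The case against.** Four points on the other side deserve weight.

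- **The analyses are exploratory.** The treatment effect comes from an intention-to-treat model, and nothing in the protocol says that dose or mode results will support a conclusion. This stands and limits the seriousness. It does not remove the bias, and no caveat accompanies the contrasts.
- **The method may be in the analysis plan.** The protocol defers statistical detail to that plan, and the subgroup sentence names no model. An unseen plan could add adjustment or a causal estimator. The missing threshold and estimator are therefore not counted as errors. What the protocol does fix is which groups are compared, and that is the problem.
- **The figures are assumed and can be small.** At 90% reaching the dose, the rate against control is only 5–7%. Facilitator clustering lowers the worst case from 27% to about 23%. The 21–89% range applies only if the ambiguous wording means a separate contrast with dyads below the dose.
- **The remedy has its own weakness.** A complier average causal effect assumes that allocation does nothing below the minimum dose. Session one already explores goals, maps them to modules and signposts services {11a}, so a partial dose may act.

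A reader might also infer that delivery mode as a whole drifts with calendar time. The protocol ties only face-to-face delivery to the lifting of restrictions; telephone or video follows preference and ability. Nor does the protocol claim a mode-specific effect against control: the mode comparison is openly within the intervention arm.

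**Conclusion.** The point holds for the exploratory analyses only. As written, they compare groups defined by treatment received, and the protocol's own account shows that dose and mode depend on preference, ability or continued participation. Such contrasts cannot isolate the effect of dose or mode.

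For dose against control, the distortion is 0.03–0.20 SD, which is 6–40% of the 0.5 SD design effect. Against those below the dose it is 0.3–0.5 SD, at the upper end as large as the design effect. Both ranges rest on the assumed compliance and prognosis gap. No size can be given for mode.

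It would be wrong to read this as a threat to the main finding, because the primary comparison keeps every dyad in its randomised arm. The change is worth making before final data are available, but it is not critical.

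**What to change.** **Dose.** Replace the minimum-dose contrast with a complier average causal effect, using random allocation as the instrument and keeping the site and facilitator terms of the primary model. The session counts it needs are already assessed in the fidelity analysis. State that it assumes no effect of allocation below the minimum dose. Check this by repeating the analysis with a lower threshold, such as any session attended, or with sessions attended as a continuous dose.

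**Mode.** Report outcome by predominant delivery mode as descriptive and non-randomised, with no claim of a mode effect. Optionally, test an arm-by-mode interaction using the mode of the consent or baseline contact before randomisation, if that mode is recorded in both arms. The protocol does not say that it is. It would only approximate delivery mode and would not capture a later move to face-to-face sessions.

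**Cost.** Revised wording and one standard extra analysis. With no access to the intervention among controls, the estimate is roughly the intention-to-treat difference divided by f. Its interval is therefore wider by about 1/f: 1.11 times at 90% and 1.67 times at 60%. In return, it is centred on zero when allocation has no effect.
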